**Discussion:**

The overall objective is to delineate the relationship between CVL-dysfunction, infection and TE. The primary aim is to evaluate the role of CVL-dysfunction as a predictor of symptomatic TE in children with cancer. We hypothesize that children with CVL-dysfunction have activation of the coagulation system resulting in an increased risk of symptomatic TE. The secondary aims are to study the impact of CVL-dysfunction on the rate of infection and the survival [OS and event free survival (EFS)] of children with cancer. We postulate that patients with CVL-dysfunction have an occult CVL-related clot which acts as a microbial focus with resultant increased risk of infection. Further, CVL-dysfunction by itself or in combination with associated complications may cause therapy delays resulting in adverse outcome.

This study will help to identify children at high risk for TE and infection. Based on the study results, we will design randomized controlled trials of prophylactic anticoagulant therapy to reduce the incidence of TE and infection. This in turn will help to improve the outcome in children with cancer.

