Central venous line (CVL) is the single most important risk factor for development of TE in children [15-29]. Long-term CVL has become an integral part of cancer-therapy in children. It has improved both the quality of care and quality of life in children with malignancy. CVLs are commonly used to deliver chemotherapy, blood products, parenteral nutrition and other intravenous therapies as well as facilitate repeated blood drawing essential for the care of these patients. However, CVLs are associated with significant complications leading to morbidity and mortality [16-29]. Two recent studies have identified a CVL-related complications rate of 40%-46% in children with cancer [18,19]. Infection and TE are the two most common and serious medical complications related to CVL and may necessitate CVL removal in ~ 20%-35% of tunneled CVLs [29].

CVL-related TE is associated with significant acute and chronic morbidity and mortality. Catheter occlusion (in 11-40% patients), loss of venous access, infection (22-40%), embolism to other vessels including PE (~13%), and subsequent development of post-thrombotic syndrome (15-35%) are commonly described morbidities in patients with CVL-associated TE [21,23,25,30]. As observed in a recent study, patients with CVL-related TE had shorter CVL life and increased number of CVLs compared to those without TE [19]. Further, CVL-related thrombi may promote TE at other sites in the body. In addition, CVL-related acute morbidities lead to loss of CVL and interruption of chemotherapy [19-31]. Using a retrospective cohort design we and others have shown an adverse impact of CVL dysfunction on survival of children with cancer [32,33].

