Deitcher et al., reported CVL-dysfunction in 28% children with brain tumors; children with CVL-dysfunction, but not with major TE, had a reduced overall survival [32]. Further, our results suggest that CVL-dysfunction is an independent risk factor for poor OS and EFS in children with cancer [33]. The poor outcome in children with cancer and CVL-dysfunction could be related to the interruption in therapy due to the loss of CVL or due to the associated complications like TE and infection. In addition, CVL-dysfunction may represent activation of coagulation system; a marker of poor prognosis in adults with cancer [32,33,36]. Thus, CVL-dysfunction probably reflects significant underlying pathology. Despite these observations there are so far no prospective studies to evaluate the clinical significance of CVL-dysfunction. Secondary aim 2 evaluates the relationship of CVL-dysfunction with OS and EFS. CVL-dysfunction may herald underlying undetected TE; the early diagnosis of which may prevent complications like overt TE, infection and therapy-delays. This in turn will improve the overall outcome in children with cancer.

#### Rationale for secondary aim 3

Although the three common complications of CVL namely CVL-dysfunction, infection and TE seem to be closely associated, the exact relationship is unclear. One retrospective study in children with cancer showed an increased risk of TE in association with CVL-dysfunction (OR 3.7, p = 0.001) and infection (OR 2.2, p = 0.016) whereas children having both dysfunction and infection had much higher risk of TE (OR 6.4, p<0.001) [17].

Presence of a local clot may lead to CVL-dysfunction as well as may act as a nidus of infection providing fertile ground for growth of the microorganisms. This may lead to either local, CVL-related infection or infection elsewhere in the body. CVL-dysfunction also needs frequent manipulations such as repeated attempts to infuse or withdraw blood; this may increase the chances of infection in immunocompromised patients. On the other hand, presence of infection can potentially initiate activation of coagulation and formation of TE in the vessel which is already damaged by CVL or by hyperosmolar infusions. The small clot developed in the process may progress to cause a significant TE either locally or distally elsewhere in the body. This clot may also lead to CVL-dysfunction.

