##### Measurement of the exposure (i.e. CVL-dysfunction)

To avoid recall bias in recording CVL-dysfunction, CVL-access information will be collected and recorded prospectively. Currently on the the inpatient unit, every time the CVL is accessed, the nurse accessing the CVL completes the CVL checklist and records any problems in blood-draw, infusion or need for tPA. Similar checklist will be filled out for patients’ outpatient visits as well as emergency room visits, if any. These checklists will be collected and reviewed by the study staff at regular intervals In addition, during the regular clinic visit patients (or care givers) will be asked about the functioning of CVL and any problems encountered and their responses documented. We believe that combination of prospective documentation by nursing staff and patient recall will capture all the events of CVL-dysfunction. The patient will be categorized as “exposed” once the patient has met the criteria for CVL-dysfunction.

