##### Sample size

The primary objectives of the study are to develop a model to discriminate between patients with and without symptomatic TE. To determine the optimal discriminant clinical model we will undertake a multivariable analysis. Simulation studies demonstrate that logistic models require 10 to 15 events per predictor to produce stable model estimates [54,55]. Based on our retrospective data and published reports we anticipate that at least 20% patients will be exposed (i.e. with CVL dysfunction) and 80% unexposed (i.e. without CVL dysfunction) [17,33,36]. Preliminary data from the retrospective study showed that the overall prevalence of TE was 11%; 23% of exposed and 9% of unexposed patients had TE. We will evaluate five predictors in our multivariable analysis. In this study, we have a fixed sample size of 450 patients (90 exposed with CVL dysfunction; and 360 without CVL dysfunction). The overall rate of symptomatic TE is assumed to be 11% (~50 events of TE) [36].

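### No order or interval is set between line dysfunction and TE, so one odds ratio mixes a sign of an existing clot with forward risk, and only the latter supports a prophylaxis target

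*Protocol article*

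**What the plan says.** Under Definitions, dysfunction needs trouble with drawing or infusing on at least two documented occasions, in the same lumen if the line has several. Under Measurement of the exposure, a child is exposed "once the patient has met the criteria for CVL-dysfunction". The Analysis plan then uses dysfunction as a yes/no factor in a logistic regression on TE yes/no. Time to dysfunction and time to TE are listed as variables, but the model described does not use them to put the two events in order. None of these sections gives a minimum interval, a landmark or a cut-off date before TE. Exclusion criterion 4 removes only dysfunction found before enrolment.

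The protocol also says that a clot can block the line. Background lists, among morbidities in patients with CVL-associated TE, "Catheter occlusion (in 11-40% patients), loss of venous access, infection (22-40"%). The rationale for secondary aim 2 says "CVL-dysfunction may herald underlying undetected TE". The rationale for secondary aim 3 names a local clot as a possible cause of dysfunction and calls the order of events unclear.

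Two uses of the result are declared. One is earlier diagnosis of a TE already present (rationale for the primary aim; Discussion). The other is prevention: "we will design randomized controlled trials of prophylactic anticoagulant therapy" (Abstract; similarly in the Discussion).

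Sample size gives a "fixed sample size of 450 patients (90 exposed with CVL dysfunction; and 360 without CVL dysfunction"), preliminary rates of "23% of exposed and 9% of unexposed patients had TE", and no target odds ratio.

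**The concern.** If a silent clot blocks the catheter and is diagnosed days later, the line failure precedes the diagnosis but not the clot. The analysis records an exposed child who went on to TE, just as it would if dysfunction had come well before any clot.

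Putting the recorded dates in order deals with dysfunction first met after a diagnosed TE, which a yes/no variable would otherwise also count. It does not deal with the silent clot.

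The two uses need different timing. A sign that is concurrent with the clot is useful for early diagnosis. A prophylaxis target needs a period after dysfunction and before TE in which something could still be prevented. A single OR cannot show which of these was found, yet the document goes from a positive result to both.

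**Working it through.** **The plan's own figures.** 450 × 0.11 = 49.5, which matches the stated 50 or so events, and 5 predictors × 10 events = 50. Applying the preliminary rates to the 90/360 split gives 0.23 × 90 + 0.09 × 360 = 20.7 + 32.4 = 53.1 events (11.8%). This is slightly above 50 and makes no difference below.

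**Implied contrast.** OR = (0.23/0.77)/(0.09/0.91) = 3.02. This is derived here; the protocol does not plan it.

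**Model with no forward effect.** Let q be the background probability of dysfunction and f the fraction of all TE patients whose line is blocked by the existing clot before diagnosis. Then

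- P(dysfunction | TE) = q + (1 − q)f
- spurious OR = [q + (1 − q)f] / [q(1 − f)]

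Two values of q are used:

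- 17.5%, the rate among children without TE in the implied table: 69.3/(69.3 + 327.6)
- 20%, the whole-cohort exposure in Sample size

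Write f = s × o. Here o is occlusion among CVL-related TE (11-40%, Background) and s is the share of all TE that is CVL-related. The documents do not give s for this cohort, so it is an assumption. The nearest figure, in Background, is that about half of symptomatic TE in children with acute lymphoblastic leukaemia lie in the central nervous system.

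| q | s | OR at o = 11% | OR at o = 40% |
|---|---|---|---|
| 17.5% | all | 1.71 | 4.82 |
| 17.5% | half | 1.33 | 2.43 |
| 20% | all | 1.62 | 4.33 |
| 20% | half | 1.29 | 2.25 |

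Example for q = 20%, s = half, o = 40%: f = 0.20, so OR = (0.20 + 0.80 × 0.20)/(0.20 × 0.80) = 0.36/0.16 = 2.25.

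**What would reach 3.02.** Solving the OR formula gives f = q(OR − 1)/(1 − q + q × OR).

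- q = 20%: f = 0.404/1.404 = 28.8%. With o at its 40% maximum, s must be at least 0.288/0.40 = 72%.
- q = 17.5%: f = 26.1%, about 14 of 53 TE. Then s must be at least 0.261/0.40 = 65%.

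**A less severe reading of 11-40%.** If the range is all occlusion seen in TE patients, background included, and every TE is CVL-related, the OR is P/(1 − P) × (1 − q)/q with P from 11% to 40%. That gives 0.58 to 3.15 at q = 17.5% and 0.49 to 2.67 at q = 20%.

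**The case against.** The strongest reply is that finding an undiagnosed clot is a declared purpose. The primary hypothesis concerns the diagnosis of symptomatic TE, and the rationale for the primary aim offers dysfunction as a surrogate that would justify further imaging. For that use, a blocked line with a silent clot is a true positive. This stands, and the planned model should be kept for that question. It does not carry over to the prevention use, which the Abstract and Discussion also draw.

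A second reply is that lag windows belong in an analysis plan that is not shown. The choice of window may well sit there. But the exposure rule, the form of the model and the conclusion are all stated here, and as stated they do not support a forward-risk reading.

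A third is that a lag has the same weakness as ordering by date, because a clot can stay silent for longer than any chosen window. That stands too: a lag reduces this bias and cannot remove it.

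A reader might infer more, namely that the protocol's own figures show the whole implied OR could be an artefact. They do not:

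- The required CVL-related share of 65-72% or more is not in the documents, and the only site figure (one cancer type) points lower.
- The 11-40% is not said to be clot-caused, to precede diagnosis, or to come from symptomatic TE. The rationale for the primary aim cites a study in which only 5 of 21 children with CVL-related TE had symptoms.
- Dysfunction must be documented twice, so not every blocked line would qualify.

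**Conclusion.** The point holds as a limit on interpretation that is worth correcting. The planned OR cannot separate a marker of existing TE from a predictor of later TE, and the prophylaxis conclusion needs the latter.

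With half of TE CVL-related, 17.5-20% background dysfunction and no forward effect, clot-caused occlusion could yield an OR of about 1.3-2.4. On the log scale that is roughly 23% (ln 1.29/ln 3.02) to 80% (ln 2.43/ln 3.02) of the implied 3.02. All of it could be explained only if about two thirds to three quarters or more of TE are CVL-related and occlusion is near 40%. These are upper values, because two documented occasions are required and the 11-40% may include background or post-diagnosis occlusion. The early-diagnosis use is unaffected.

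**What to change.** 1. Keep the planned logistic analysis and label it as answering the marker and early-diagnosis question.
2. Report the distribution of days from meeting the dysfunction criterion to onset of TE symptoms. The article does not name the onset date as a data item, so confirm that the TE form captures it.
3. Add a time-to-event analysis of TE, a form of the outcome that the Analysis plan already lists. Enter dysfunction as a time-dependent exposure that counts only before TE. As a sensitivity analysis, lag it, for example by 7 days, with 3 and 30 days as alternatives. These windows are a choice and come from no figure in the documents.
4. State in advance how TE inside the lag is handled, for example reported separately as concurrent and censored. Counting it as an unexposed event would bias the estimate towards no effect. The days inside the lag should likewise not be credited to the unexposed group.
5. Rest any statement about a prophylaxis target on the lagged estimate, and say that long-silent clots may still bias it.

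No new visits or tests are needed, since line access and TE are recorded prospectively. It is more than a change of wording, because it adds a second model. It also costs precision: about 0.23 × 90 ≈ 21 exposed TE are expected before any lag, so the lagged estimate will rest on fewer and have a wider confidence interval.

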##### Data documentation and retrieval

All five participating institutions will use the CVL access and function check list. Our research staff will train the health care professionals for documentation and collection of primary and secondary outcome data. Data will be collected in real time by chart review and review of ancillary material (e.g. line function checklist).

##### Analysis plan

The analysis and reporting of the study will be performed in accordance with the STROBE Statement [50]. The primary outcome is a binary variable- symptomatic TE (presence/absence) as well as a continuous variable (time to event). Independent variables include: age, number of catheter days and time to CVL-dysfunction as continuous variables and, gender (male/female), cancer type, CVL-dysfunction (presence/absence), symptomatic TE (presence/absence), infection (presence/absence) as categorical variables. The process of participant recruitment and retention will be summarized using a flow diagram. Analysis results of participant recruitment and retention will be summarized using descriptive summary measures: mean (standard deviation) or median (minimum-maximum) for continuous variables; and number (percent) for categorical variables. We will use logistic regression analysis to determine the factors that can best discriminate between the two patient groups (i.e. those with and without TE). The list of potential factors is determined *a priori* and includes age of the patient at the time of diagnosis of cancer, cancer type; CVL-dysfunction (presence/absence), infection (presence/absence) and CVL type (internal/external). Univariate analyses will be performed to determine which variables to include in the multivariable models using the criterion of alpha = 0.20. Initially, we will use complete case analysis (i.e. do the analysis without taking missing data into account) and then repeat the analyses with missing data handled by multiple imputation technique [51-53].

For regression models, we will report the OR (for logistic regression), corresponding standard error, 95% confidence intervals and associated p-values. We will report P-values to 3 decimal places with p-values less than 0.001 reported as p<0.001. For all tests, we will use alpha =0.05 level of significance. Examination of residuals will provide an assessment of model assumptions for regression analyses. Goodnees-of-fit for the models will be performed using appropriate Hosmer-Lemeshov tests. For multivariable regression analysis, we anticipate multicolinearity [54]. We will assess colinearity using the variance inflation factor (VIF) which measures the extent to which the variance of the model coefficients will be inflated (because of the correlation of the variable with other predictor variables) if that variable is included in the model. Variables with VIF >10 will be considered colinear and will be excluded from the analysis [55].

The discriminant performance of the model will be evaluated using sensitivity, specificity and the area under the ROC – receiver operating characteristic curve. We will use bootstrapping approach to internally validate the model. We will compare the performance characteristics (i.e. sensitivity, specificity, area under the ROC curve, etc) between the original model and the bootstrap model. OS and EFS will be estimated using Cox-regression which will allow for adjustment of confounding variables. Hazard ratio (HR) will be calculated using log-rank method.

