Do children with CVL dysfunction have increased risk of symptomatic thromboembolism compared to those without CVL dysfunction, while on cancer therapy?

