In summary, the cause and effect relationship of infection as well as the chronological relationship of infection, TE and CVL-dysfunction are still unclear. Figure 1 outlines our proposed hypothesis of the mechanism of interaction of these three CVL-related complications.

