#### Recruitment and consent process

Newly diagnosed cancer patients will be identified through pediatric oncology services at the participating institutions. Study staff will review patients’ records to determine eligibility for the proposed study. Eligible patients will be approached, prior to CVL placement or within two weeks of CVL placement, for informed consent. Reasons for non-participation will be recorded for all screened patients.

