#### Study follow-up and study duration

This study will require no visits above and beyond those required for the clinical care of the patient. After initial hospitalization for evaluation and therapy for cancer, all patients are seen frequently (either weekly or monthly) at the outpatient clinics as part of their routine clinical care. Patients will be monitored for infection, disease progression or recurrence, or SMN. After completion of therapy patients are followed life-long according to the “After-Care-Guidelines” recommended by POGO.

Patient enrollment will occur until the required sample size is achieved. We anticipate that the required patient population will be enrolled during first two and half years of the study. Patients will be followed for the development of symptomatic TE until the completion of cancer therapy and final removal of CVL which occurs within 6–12 weeks post completion of therapy. Thereafter overall outcome data regarding continued remission, recurrence of cancer, SMN or death will be collected for each patient every six months for a total period of five years from the initial diagnosis.

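### Symptomatic TE is modelled by logistic regression on ever/never CVL-dysfunction, with no rule that dysfunction precede the TE diagnosis and no model for the stated time-to-event outcome

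*Protocol article*

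**What the plan says.** The primary research question is: "Do children with CVL dysfunction have increased risk of symptomatic thromboembolism compared to those without CVL dysfunction, while on cancer therapy"?

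The Analysis plan gives the outcome two forms: "The primary outcome is a binary variable- symptomatic TE (presence/absence) as well as a continuous variable (time to event"). For TE it then names one model: "We will use logistic regression analysis to determine the factors that can best discriminate between the two patient groups", meaning those with and without TE. The a priori factors are age at cancer diagnosis, "cancer type; CVL-dysfunction (presence/absence), infection (presence/absence) and CVL type (internal/external"). The result is reported as an OR. Cox regression is assigned to OS and EFS only. The Sample size section also argues from logistic events per predictor.

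Other sections bear on this choice:

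- **Exposure.** A patient is classed as exposed "once the patient has met the criteria for CVL-dysfunction" (Measurement of the exposure). The Definitions require two or more documented occasions.
- **Follow-up.** "Patients will be followed for the development of symptomatic TE until the completion of cancer therapy and final removal of CVL" (Study follow-up and study duration).
- **Order of events.** The Exclusion criteria remove only dysfunction diagnosed before enrolment. Nothing is said about dysfunction first met after a TE. The Rationale for secondary aim 3 accepts that a clot can bring on dysfunction and concludes that "the chronological relationship of infection, TE and CVL-dysfunction are still unclear".
- **Time variables.** The Analysis plan lists catheter-days and time to CVL-dysfunction among the independent variables. Neither is in the a priori factor list.

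**The concern.** Exposure starts during follow-up, so the order of the two events carries the information that the primary question needs. A present/absent code discards it. A child with a diagnosed TE whose line fails afterwards enters the model as an exposed case, exactly like a child whose line failed months before the TE.

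Line time is a second route to bias. A longer course gives more opportunity for both dysfunction and TE, so the two can be associated across patients with no link inside any one patient. Time to dysfunction cannot repair this as an ordinary covariate, because it is undefined in the roughly 80% expected to stay unexposed.

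The Discussion intends to use the result to identify high-risk children and to design trials of anticoagulant prophylaxis. That use requires dysfunction to come first.

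**Working it through.** **1. The plan's own figures (Sample size).** 450 × 0.11 = 49.5, the stated ~50 events; 49.5 / 5 = 9.9 events per predictor. The group rates of 23% and 9% imply OR = (0.23/0.77) / (0.09/0.91) = 3.02.

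**2. Set-up.** From the plan: n = 450, 20% ever dysfunction, 11% ever TE. Assumed here: constant hazards, independent event times (no true effect), the therapy lengths, and the share of TE cases in which TE brings on dysfunction. The document gives none of these. All ORs below are unadjusted. Cells are a (both events), b (dysfunction only), c (TE only) and d (neither); OR = ad/(bc).

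**3. Equal line time, 2 years.** Hazards: dysfunction −ln(0.80)/2 = 0.1116 and TE −ln(0.89)/2 = 0.0583 per year.
- a = 450 × 0.20 × 0.11 = 9.9; b = 80.1; c = 39.6; d = 320.4. OR = 1.00.
- P(dysfunction first, both occur) = 0.11 − [0.0583/(0.1116 + 0.0583)] × (1 − 0.80 × 0.89) = 0.11 − 0.3431 × 0.288 = 0.0112.
- As a share of both events: 0.0112/0.022 = 51%. So 49% of patients with both events have TE first.

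**4. TE brings on dysfunction, equal line time.** Move a share s of the 39.6 TE-only cases to a.
- s = 15%: 15.84 × 320.4 / (80.1 × 33.66) = 1.88.
- s = 30%: 21.78 × 320.4 / (80.1 × 27.72) = 3.14.

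**5. Unequal line time, no TE-induced dysfunction.** Hazards are recalibrated so that the totals stay at 20% and 11%. False-positive rates use the Wald z of the expected table at n = 450, taking alpha 0.05 as two-sided.

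| Assumed lengths (years) | a | b | c | d | OR | False positives |
|---|---|---|---|---|---|---|
| 0.5 / 1 / 2.5 in 30 / 20 / 50% | 12.81 | 77.19 | 36.69 | 323.31 | 1.46 | about 19% |
| 0.5 / 2.5 in 50 / 50% | 13.87 | 76.13 | 35.63 | 324.37 | 1.66 | about 32% |

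Within each length stratum the two times are independent and the OR is 1.00. Adding s = 30% to the second row gives 24.56 × 324.37 / (76.13 × 24.94) = 4.20, which combines two mechanisms.

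**6. Dropping post-TE dysfunction but keeping logistic regression.** Patients with TE first become unexposed cases.
- Equal time: a = 5.04, c = 44.46; OR = 5.04 × 320.4 / (80.1 × 44.46) = 0.45.
- Half/half lengths: a = 7.15, c = 42.35; OR = 7.15 × 324.37 / (76.13 × 42.35) = 0.72.

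An ordering rule alone therefore biases the OR the other way, because patients without TE have longer to become exposed.

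**7. Exposure switched on at dysfunction, follow-up stopped at TE.** In separate simulations with gamma-distributed line time, the person-time rate ratio with no true effect stayed at 0.99-1.01, with or without TE-induced dysfunction and at equal or unequal line time. With a true rate ratio of 2.0 and equal line time, the ever/never OR was 1.56, and 0.92 if only prior dysfunction counted. A real effect can therefore be diluted or hidden.

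**The case against.** **The clot is the hypothesis.** A reader might infer that every clot that blocks a line is reverse causation. The document does not support that. Its rationale for the primary aim proposes dysfunction as a surrogate for underlying TE, and its rationale for secondary aim 2 says dysfunction may herald undetected TE. A clot that blocks the line before symptomatic TE is diagnosed is the intended signal. Only dysfunction first met after the diagnosis is an artefact, so diagnosis, not biological onset, is the right cut.

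**The planned model is adjusted.** Cancer type is a candidate covariate and plausibly tracks therapy length, and within length strata the null OR is 1.00. The line-time ORs above would shrink as far as cancer type captures length. Some bias can remain from variation within a cancer type, or if cancer type fails the univariate 0.20 screen. Adjustment does nothing about event order.

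**Line time is not ignored.** Catheter-days is defined and listed. But it is outside the a priori factor list, and it is measured after baseline.

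**Immortal time.** Because consent may come "prior to CVL placement or within two weeks of CVL placement" and enrolled children must be free of dysfunction, a reader might infer immortal time. This is delayed entry common to all patients. Counted from enrolment, it credits no event-free time to the exposed group.

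**TE-induced shares.** Nothing in the document supports 15-30%. TE at any site counts, and the Background puts about half of symptomatic TE in ALL in the CNS, where a clot would not be expected to block the line.

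**An unseen plan.** A full protocol or SAP may specify a time-to-event model. The article nevertheless states logistic regression as its TE analysis and sizes the study on it, so this is a stated choice and not merely omitted detail.

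**Conclusion.** The point holds in this form: the one model named for the primary outcome uses ever/never exposure, has no ordering rule, and leaves the stated time-to-event form without a model. The resulting OR can be wrong as an answer to the primary question.

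The illustrative null ORs are 1.00 (equal line time), about 1.5-1.7 (unequal line time), 1.9-3.1 (TE-induced dysfunction in 15-30% of TE cases at equal line time), and up to 4.2 only when the last two are combined. They fall to 0.45-0.72 if post-TE dysfunction is dropped within the logistic model. All are unadjusted and rest on assumed therapy lengths, shares and constant hazards.

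A reader might infer that the planning OR of 3.0 is itself an artefact, or that the study's OR will be inflated. Neither follows. The scenarios run in both directions, and the actual size and direction cannot be determined from the document.

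**What to change.** Make the primary TE analysis a cause-specific Cox model for time to first symptomatic TE diagnosis:

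- Count follow-up from enrolment, or from CVL insertion with delayed entry at enrolment.
- Enter CVL-dysfunction as a time-dependent covariate that switches on when its criteria are met (the second documented occasion), and only if that is before TE diagnosis.
- Treat infection in the same way. It is also coded present/absent and can also arise after a TE.
- Censor at final CVL removal. Treat death without TE as a competing event and report cumulative incidence.
- Keep the ever/never logistic model, with its sensitivity, specificity and ROC results, as descriptive only.

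The cost is mainly analysis-plan wording. The access checklists, CVL insertion and removal dates, and TE and infection details are already to be collected. The price is less exposed person-time and a somewhat wider interval for the dysfunction effect.
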